## Abstract

**Background:**

Physical activity affords a wide range of physiological and psychological benefits for children and adolescents, yet many children with physical disabilities are insufficiently active to achieve these benefits. The StepUp program is a newly developed 6-week pedometer-based self-management program for children and adolescents with physical disability. Participants use a pedometer to undertake a 6-week physical activity challenge, with personalised daily step count goals set in consultation with a physiotherapist. The study aims to evaluate the effectiveness of the StepUp program, using a randomised control trial design.

**Methods/design:**

A target sample of 70 young people with physical disabilities (aged 8–17 years, ambulant with or without aid, residing in Adelaide) will be recruited. Participants will be randomly allocated to either intervention or control following completion of baseline assessments. Assessments are repeated at 8 weeks (immediately post intervention) and 20 weeks (12 weeks post intervention). The primary outcome is objective physical activity determined from 7 day accelerometry, and the secondary outcomes are exercise intention, physical self-worth, quality of life and fatigue. Analyses will be undertaken on an intention-to-treat basis using random effects mixed modelling.

**Discussion:**

This study will provide information about the potential of a low-touch and low-cost physical activity intervention for children and adolescents with cerebral palsy.

**Trial registration:**

Australian New Zealand Clinical Trials Registry (ANZCTR): ACTRN12613000023752.

## Background

Physical activity affords wide-ranging physiological and psychological benefits for children and adolescents, regardless of disability status [1]. However, regular participation in physical activity appears to hold important additional benefits for individuals with physical disabilities. For example, evidence is emerging that physical activity is vital for prevention of deterioration in physical function and independence in young and middle aged adults with cerebral palsy [2-4]. Furthermore, physical activity plays a key role in the management of chronic health conditions such as asthma [5] and heart disease [6], and these are common comorbidities in children with physical disabilities [7].

Up to 3.7% of Australian children have a physical disability [7], in many cases affecting their ability to participate in everyday life. Therapy and health services for young people with disabilities have traditionally focussed on secondary prevention. A focus on physical activity, per se, for young people with physical disabilities is a relatively fledgling field of research. Recent research has shown that young people with cerebral palsy and other physical disabilities are less physically active than their non-disabled peers [8,9]. It is also clear that young people with disabilities tend to participate in lower intensity physical activities compared with children without disabilities [10].

To date, just a handful of physical activity interventions for young people with disabilities have been reported in the scientific literature [11-14]. Ideally, such programs need to be flexible, in order to accommodate the wide range of participants’ gross motor abilities and interests. Additionally, young people with physical disabilities are often geographically dispersed and face transport barriers, therefore programs which can be undertaken without intensive face-to-face contact with therapists or fitness instructors are advantageous. Furthermore, programs requiring minimal equipment and staffing resources offer considerable potential to be incorporated into ongoing services provided by therapists and health providers.

Pedometers are small devices, typically worn on the waist band which measure step counts [15]. Pedometer-based interventions are a simple and effective means of increasing physical activity, with a recent systematic review of pedometer-based interventions in youth without disabilities finding that 12 out of 14 studies produced significant increases in physical activity [16]. Furthermore, development of self-management skills is believed to enhance well-being, self-determination and participation in health care, ultimately leading to improved health outcomes, as well as reduced health care utilisation (and associated costs) [17]. To address these issues, we have developed a six-week self-management, pedometer-based physical activity program for young people with physical disabilities, titled “StepUp”.

This study aims to evaluate this new six-week pedometer-based self-management program for ambulant children and adolescents with physical disabilities. Specifically, it aims to determine (a) whether the program is effective in increasing physical activity over the course of the 6 week intervention and at longer-term follow up, (b) whether the program impacts physical self-worth, exercise intention, pain and fatigue and quality of life, and (c) the program’s acceptability and engagement.

## Methods/design

### Study design

The StepUp study is a two group (StepUp intervention versus standard care) randomised controlled trial with data collection at three time points; at baseline, end of intervention (8 weeks post baseline) and follow up (20 weeks post baseline; 12 weeks post end of intervention). Ethical approval for the study has been granted by the University of South Australia Human Research Ethics Committee and the study protocol has been registered with the Australian and New Zealand clinical trials registry and assigned the protocol number: ACTRN12613000023752.

### Study sample

The study will aim to enrol 50–70 participants. Participants are being recruited through Novita Children’s Services, the major provider of community-based therapy, equipment and family support services to young people with disabilities and special needs aged 0–18 years in the state of South Australia. Novita clients are eligible to participate if they (1) have a physical disability, (2) are aged 8–17 years, (3) have mild-to-moderate levels of physical disability (able to ambulate in the community with or without assistance; Gillette Functional Assessment Questionnaire levels 7, 8, 9 or 10 [18]), (4) live in or near Adelaide, Australia, and (5) are considered by their parent to have cognitive ability to understand the program. Exclusion criteria are (1) recent or planned medical and/or orthopaedic intervention (e.g. surgery or botulinim toxin injections) impacting ability to be physically active, and (2) injury impacting on ability to partake in physical activity. Recruitment is taking place on a rolling basis from June to December 2013.

### Procedure

Potential participants identified from the Novita client database are being sent an informative invitation letter. Participants and their parents are required to give written informed consent to be involved in the study.

### Outcome measures

Assessments are being conducted at three data collection time points (baseline, week 8 and week 20). The baseline assessment is conducted face-to-face at four sites located throughout metropolitan Adelaide, while the 8 week and 20 week assessments are conducted via the post. Assessments are delivered by non-blinded research personnel, however, there is minimal potential for bias given that the outcome measures are self-administered (i.e. surveys) by participants. Research personnel have been trained in the need to deliver the outcome measures in an impartial manner. Participants who complete all three assessments will receive $50 honoraria in recognition of the time and effort involved in undertaking the accelerometry and survey assessments.

At each assessment point, participants will complete the following measures:

1. Primary outcome: objective physical activity.

Objective physical activity is being assessed using Actigraph GT3X + accelerometers (ActiGraph, Pensacola, FL). The accelerometer is worn at the waist on an elasticized belt, on the right mid-axillary line. Participants are requested to use a wear-time log sheet to record time the device is put on and removed, as well as sleep and nap times. Since other studies have reported problems with meeting minimum-wear-time requirements with a waking hours protocol (i.e. daily instrument removal for sleep), participants are encouraged to wear the accelerometer 24 hours per day for 7 consecutive days. Accelerometers are initialized using ActiLife software [19], with an epoch length of 1 second and sampling rate of 80 Hz. Accelerometers are returned to the study site by reply-paid mail, at which time the research team verify the data for completeness using ActiLife software. Sixty minutes of consecutive zeros is being used to define invalid minutes (i.e. minutes in which the accelerometer was not worn). The minimal amount of accelerometer data that is considered acceptable is 4 days, including at least one weekend day, with at least 10 hours of valid wear time per day. If accelerometer data are incomplete, participants are asked to wear the accelerometer for an additional 7 days (to a maximum of 14 days) to ensure that the minimal data requirements are met. Accelerometers have been shown to accurately measure physical activity in children with physical disabilities (e.g. see [20,21]).

2. Secondary outcomes:

a. Exercise intention is being assessed using the LEAP II Exercise Intention Scale [22]. This scale was originally designed for 5th – 8th grade children. It examines intention to be physically active, and consists of four items rated on a 5-point scale, which are averaged to produce a single “Exercise Intention” score, ranging between 1 and 5, with a higher score indicating higher intention to be active. The factorial validity of this scale has been confirmed [22] and the scale has been used previously with children with cerebral palsy [11].

b. Physical self-worth is being assessed using the Physical Self-Worth Scale [23]. The scale contains 6-items, each scored from 1 to 4 (with 1 = 'very low’ self-worth and 4 = 'very high’ self-worth). Test-retest in 7th and 8th graders has been shown to be high (ICC = 0.86). The scale has been shown to correlate with physical fitness test scores to varying degrees (*r* = 0.23 - 0.57) [24] in adolescents without disability.

c. Quality of life (QOL) is being assessed using the KINDL [25], a generic QOL instrument designed for children aged 8–16. This 24 item scale records QOL in six dimensions, with the subscale scores combining to produce a total score. The KINDL has been shown to have moderate-to-high internal consistency (0.63 < α < 0.84), moderate convergent validity with other QOL instruments [25].

d. Fatigue is being assessed using the PedsQL Multidimensional Fatigue scale [26]. This generic instrument for children aged 5–18 contains 18 items assessing fatigue in three dimensions (general fatigue, sleep/rest and cognitive fatigue), with subscales tallied to produce an overall fatigue score. It has been demonstrated to have excellent reliability and construct validity in a variety of paediatric patient populations [26-28].

The surveys (outcome measures 2a-2d) are being delivered in pen and paper format.

### Randomisation

Random allocation to the intervention or control condition will take place after participants have completed all aspects of their baseline assessment.

Since age is recognised to impact children’s activity levels [29], and impairment level is associated with activity level in children with physical disabilities [9], a stratified randomised allocation procedure is being used to ensure an even balance of age and impairment levels between groups. Given the recognised effect of season on physical activity [30], blocking is being employed to ensure a close balance of participants in the intervention and control conditions throughout the study period, as recommended by CONSORT [31].

Randomisation is being achieved using four sets of opaque envelopes (Set 1: ages 8–12 years, Gillette level 7 or 8; Set 2: ages 13–17 years, Gillette level 7 or 8; Set 3: ages 8–12 years, Gillette level 9 or 10; Set 4: ages 13–17 years, Gillette level 9 or 10). Each set includes six envelopes, with three containing control allocation, and three containing intervention allocation. Randomisation is being undertaken by CM, who is provided with the participants’ ID number, age, and Gillette level, and who has no direct contact with participants.

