### Analysis

A priori power analyses indicate that a sample of 42 will be required to detect a medium size within-between group interaction (f = 0.20), while a sample of 74 will be required to detect a small-medium size within-between group interaction (f = 0.15), assuming three repeated measures, two groups, an alpha-level of 0.05 and power of 80%. The change in outcomes from baseline to 8 weeks and 20 weeks, within and between groups, will be analysed using random-effects mixed-modelling, on an intention-to-treat basis. The relationship between primary and secondary outcomes and demographic variables will be assessed and where relationships exist the demographic variables will be used as covariates.

Data from the feedback survey and engagement data will be analysed descriptively. In addition, sub-group analysis will be undertaken to determine whether the intervention effectiveness is related to engagement/adherence.

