## Discussion

Physical activity is important for physical and psychological health, as well as for maintenance of physical function and independence in young people with physical disabilities. Despite this, there have been few rigorous studies aimed at intervening on physical activity in this population.

This project will evaluate the effectiveness of a novel pedometer-based physical activity self-management program for young people with physical disability.

Strengths and weaknesses of the StepUp study warrant discussion. The StepUp intervention has been carefully designed by a team of researchers and clinicians, which includes researchers with expertise in physical activity measurement, physical activity intervention, childhood physical disability, the development of written materials for children with learning difficulties, as well as highly experienced clinicians (physiotherapists and a psychologist). The program has been specifically designed to be low-cost and low-touch in nature, so that if it is found to be effective, it can be readily incorporated into ongoing clinical services. A strength of the study is that it involves a rigorous randomised controlled trial design, incorporating high quality outcome measures, including objective measurement of physical activity. The StepUp study is a single-site study. For budgetary and feasibility reasons, the study can only sample from a finite population (young people with physical disabilities meeting the eligibility criteria, including residing in Adelaide). We intend to invite the entire eligible population, and anticipate 40–70 participants will join the study, with a priori power analyses suggesting a sample of this magnitude should be sufficient to detect small to moderate effects, should they be present. For budgetary reasons, the follow up is only 20 weeks from baseline (12 weeks post end of intervention). Should the results of this study be affirmative, in the future it would be beneficial if the intervention could be evaluated in a larger sample, and over a longer-term period, in a multi-centre trial.

This study forms an early attempt at developing and evaluating a feasible physical activity intervention for children with physical disabilities, and findings will inform future efforts in this field, to assist young people with disabilities to achieve the benefits of physical activity.

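### Season is balanced by blocking but is not named in the analysis model, which costs some precision, mainly at week 20, without causing bias

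*Protocol article*

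**What the plan says.** The Randomisation section of the protocol article accepts that season affects physical activity, which is the primary outcome, and gives blocking as the remedy: "Given the recognised effect of season on physical activity [30], blocking is being employed to ensure a close balance of participants". The blocks sit inside four strata formed by age group and Gillette level ("Randomisation is being achieved using four sets of opaque envelopes"), and their composition is fixed: "Each set includes six envelopes, with three containing control allocation, and three containing intervention allocation".

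The Study sample section gives the entry period: "Recruitment is taking place on a rolling basis from June to December 2013". Outcome measures places assessments at baseline, week 8 and week 20. The planned size differs by section: "A target sample of 70 young people with physical disabilities" (Abstract), "The study will aim to enrol 50–70 participants" (Study sample) and "anticipate 40–70 participants will join the study" (Discussion).

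The Analysis section specifies a random-effects mixed model for change to weeks 8 and 20. On covariates it says that relationships between outcomes and demographic variables will be examined, and "where relationships exist the demographic variables will be used as covariates". Season, enrolment date, assessment date and block are not mentioned there.

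**The concern.** The design treats season as important enough to block for, yet the stated model makes no use of it. Balancing a prognostic factor by design and then omitting it from the model leaves its variance in the residual, and the reported standard error does not reflect the balance achieved.

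With rolling entry over about seven months, the seasonal component of change is not the same for every child. One who enters in June is followed from winter into spring. One who enters at the end of December is followed from summer into autumn. A visit effect shared by all children can absorb only the average of these shifts.

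At stake is precision for the primary outcome in a trial of 50 to 70 children, chiefly for the longer-term follow-up that the trial's first aim includes.

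**Working it through.** **1. The plan's own sample sizes.** For the within-between interaction with k = 2 groups and m = 3 measures, λ = N·f²·m/(1 − ρ), df1 = (k − 1)(m − 1) = 2 and df2 = (N − k)(m − 1). The correlation ρ is not stated; ρ = 0.5 and sphericity are assumed.
- N = 42, f = 0.20: λ = 42 × 0.04 × 3/0.5 = 10.08, power 0.803.
- N = 74, f = 0.15: λ = 74 × 0.0225 × 3/0.5 = 9.99, power 0.806.
- N = 70, f = 0.15: λ = 9.45, power 0.782.

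Both stated sizes reproduce.

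**2. Assessment dates.** Entry from 1 June to 31 December 2013, plus 56 and 140 days:
- Week 8: 27 July 2013 to 25 February 2014.
- Week 20: 19 October 2013 to 20 May 2014.

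**3. Time to fill a block.** With equal strata and even accrual over M months, a block of six takes 6/(N/4) × M = 24M/N months.

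| N | M = 6 | M = 7 |
|---|---|---|
| 70 | 2.1 | 2.4 |
| 50 | 2.9 | 3.4 |
| 40 | 3.6 | 4.2 |

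A stratum holding 15% of children would need 6 × 7/(0.15 × 70) = 4.0 months at N = 70, and 5.6 at N = 50.

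**4. What blocking still achieves.** In simulation of the stated scheme, the SD of the between-arm difference in mean enrolment date is about 0.25 months (N = 70) and 0.37 (N = 50). Under simple randomisation it is about 0.48 and 0.57.

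**5. How seasonal change varies with entry date.** Assume activity carries A·cos(2π(t − 0.5)/12), with t in months from 1 January (peak in mid-January), and A in units of the residual SD of one measurement. The change over d months is −2A·sin(πd/12)·sin(2π(t − 0.5 + d/2)/12), with d = 8/4.345 = 1.84 or 20/4.345 = 4.60.
- Week 20: +0.76A for entry on 1 June, +1.87A (the maximum) for early August and −1.51A for 31 December. With entry uniform from June to December, the variance of this shift is 1.11A².
- Week 8: between −0.28A and +0.93A, variance 0.133A².

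The residual variance of a change score is 2 in these units. Season's share of change variance is therefore vA²/(vA² + 2). For A = 0.25, 0.5 and 1 this gives 0.4%, 1.6% and 6.2% at week 8, and about 3%, 12% and 36% at week 20.

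**6. Effect on the standard error.** Without a season term the SE is about 2√((2 + vA²)/N). At N = 70, week 20, A = 1 this is 2√(3.11/70) = 0.42; with no seasonal variance it is 2√(2/70) = 0.338. Simulation with 3,000 runs per setting, stratified blocks of six, and annual cosine and sine terms in the adjusted model:

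| N = 70 | A = 0.25 | A = 0.5 | A = 1 |
|---|---|---|---|
| Week 8, SE without v with | 0.338 v 0.339 | 0.340 v 0.339 | 0.347 v 0.338 |
| Week 20, SE without v with | 0.343 v 0.339 | 0.360 v 0.340 | 0.419 v 0.338 |

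The excess is at most about 3% at week 8 (0.347/0.338 = 1.03). At week 20 it is about 1%, 6% and 24%.

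**7. Conservatism.** At N = 70, week 20, A = 1, the unadjusted estimate has an actual SD of 0.374 against a reported SE of 0.419; the adjusted estimate has an actual SD of 0.344. At A = 0.5 these figures are 0.351, 0.360 and 0.344. Much of the drop in the reported SE thus removes conservatism, and the rest is a true gain in precision.

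**8. Cost if season matters little.** At N = 50, week 8, A = 0.25, the SE is 0.399 without and 0.403 with the two terms, about 1% more.

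**The case against.** The strongest reply is that this is an efficiency preference, not an error. Several parts of it stand.

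- **No exclusion.** A reader might infer that the plan bars season from the model. It does not: the Analysis section names demographic covariates and excludes nothing, and an analysis plan that is not shown could add season. What remains is that the article does fix a covariate rule, and that rule omits the one time-related factor its own design singles out.
- **No bias.** A reader might infer that seasonal drift distorts the comparison. Controls are randomised and concurrent, so it does not.
- **Not all seasonal variation is left over.** A visit effect, which I assume the model contains, takes out the average shift.
- **Blocking works reasonably well.** The article promises close balance over the study period, not within each month. Four strata filling in parallel average out, so the span of one block overstates the imbalance. Chance imbalance in mean enrolment date is roughly halved.
- **The size is assumed.** No passage gives a seasonal variance. At week 8 the gain is essentially nil unless the amplitude is large. The adjusted simulation fitted the same annual shape that generated the data, which is a best case.

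A further objection is that season overlaps with visit, since later visits fall later in the year. That overlap affects the visit effect more than the between-arm difference at each visit, which is the contrast of interest.

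**Conclusion.** The point holds as one of efficiency. The protocol balances season by design, but the model it describes does not use season. The cost is some precision and slightly conservative standard errors; the treatment comparison stays unbiased.

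On the assumed amplitudes the loss at week 8 is between nil and about 3% of the SE. At week 20 it ranges from about 1% to about 24%, and the upper figure needs a seasonal amplitude as large as the residual SD of a single measurement. These figures rest on an annual cosine peaking in mid-January, even entry over seven months, equal strata and independent residuals.

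School term might seem to belong with this point, but the protocol names season only, so its omission is not an inconsistency.

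**What to change.** In the Analysis section, pre-specify a low-dimensional, time-varying season term in the primary mixed model, computed from the date of each accelerometer wear period. Day length is one option; an annual cosine and sine pair is another. Include it whatever its observed association with the outcome, so that the choice does not depend on the data. Keep the blocking as it is. A school-term indicator may be added but is optional.

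The cost is one sentence of text and one or two degrees of freedom. The wear log and the accelerometer already supply the dates, so no new data or participants are needed. If season has no effect, the loss is negligible: a simulation at N = 60 with a single binary entry-date covariate put it at about 0.5 percentage points of power.
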